#### Information only

The information only group will be conducted at participants’ homes or preferred location with access to a computer. Participants will be asked to view an 8 minute online DVD and three fact sheets relating to sun-protective behaviour which are currently available from Cancer Council Queensland’s website. The DVD is aimed at providing practical advice to adults to reduce their risk of developing skin cancer through prevention and early detection. Topics include skin cancer, types of skin cancers, means of protecting against sun exposure, UV index, and early detection including self-examination. The fact sheets cover the topics of skin cancer, sunscreen, and myths about sun protection. Participants will be asked to confirm that they had read all three fact sheets.

#### Control

Control participants will not be required to do anything beyond completing the three online surveys.

### Study and data integrity

The study design will be guided by the CONSORT (Consolidated Standards of Reporting Trials) statement [39].

### Measures

Data will be collected by self-reported pre- and post-intervention questionnaires developed by the researchers and using standard TPB items. The pre-intervention questionnaire will take approximately 15-20 minutes to complete and will be completed online immediately before the online intervention or information only session.

The post-intervention questionnaires will be completed online immediately following the intervention and at one week and four weeks after the intervention. The post-intervention questionnaires will assess the same constructs as Questionnaire 1, plus an additional set of questions which measure exposure to other sun-protective behaviour materials or promotions in the preceding week (Questionnaire 2) and month (Questionnaire 3).

#### Variables

Demographic data collected pre-intervention will include age (in years), sex (male or female), and postcode. Data will also be collected on colour of skin before tanning (pale white skin, white skin, light brown skin, moderate brown skin, deep dark brown to black skin), colour of skin with repeated exposure to the sun without protection (get no sun tan at all or occasionally get freckled, get mildly or occasionally tanned, get moderately tanned, go very brown and deeply tanned), natural hair colour (black, dark brown, light brown, dark blonde, light blonde, red), eye colour (dark brown, light brown, green, blue), number of hours per week of work conducted outdoors, and hours spent in the sun in the past week. Data relating to level of confidence using computers and frequency of accessing health information on the internet will also be gathered.

#### Outcome measures

Primary outcomes variables will assess the effectiveness of the online intervention in improving participants’ self-reported sun-protective intentions and behaviour.

The target behaviour is “performing sun-protective behaviours (i.e., using SPF 30 + sunscreen, wearing protective clothing such as a hat, long-sleeved shirt and sunglasses, and seeking shade between 10 am and 3 pm) every time you go in the sun for more than 10 minutes during the next week” (Table 1).

**Table 1 T1:** Primary and secondary outcome measures

**Variable**	**Number of items**	**Scale**	**Measurement strategies**
**Primary outcome variables**			
Intentions	3	1 (strongly disagree) to 7 (strongly agree)	“I intend to perform sun-protective behaviours.”; “I plan to perform sun-protective behaviours.”; “It is likely that I will perform sun-protective behaviours.”
Behaviour	3	1 (never) to 7 (always)	“Think about the past week. In general, how often did you perform sun-protective behaviour?”; “Think about the past week. On average, how often did you perform sun-protective behaviours on Saturday and Sunday?”; “Think about the past week. On average, how often did you perform sun-protective behaviours on a typical week day?”
**Secondary outcome variables**			
Attitudes	6	1 (pleasant) to 7 (unpleasant)	“Performing sun-protective behaviours every time I go in the sun for more than 10 minutes during the next week, would be…” (reverse scored)
		1 (good) to 7 (bad)	
		1 (wise) to 7 (unwise)	
		1 (easy) to 7 (difficult)	
		1 (nice) to 7 (awful)	
		1 (positive) to 7 (negative)	
Subjective Norms	3	1 (strongly disagree) to 7 (strongly agree)	“Those people who are important to me would want me to perform sun-protective behaviours.”; “Most people who are important to me would approve of me performing sun-protective behaviours.”; “Most people who are important to me would think that I should perform sun safe behaviours.”
Perceived Behavioural Control	4	1 (strongly disagree) to 7 (strongly agree)	“I have complete control over whether I perform sun-protective behaviours.”; “It is mostly up to me whether I perform sun-protective behaviours.”; “If I wanted to it would be easy for me to perform sun-protective behaviours.”; “I am confident that I could perform sun-protective behaviours.”
Group Norms	4	1 (strongly disagree) to 7 (strongly agree)	“Most of my friends perform sun-protective behaviours.”; “My friends think that performing sun-protective behaviours is a good thing to do.”; “How many of your friends would think that performing sun-protective behaviours every time you are out in the sun for more than 10 minutes in the next week is a good thing to do?”; “How many of your friends would perform sun-protective behaviours every time they are out in the sun for more than 10 minutes during the next week?”
		1 (none) to 7 (all)	
Personal Norms	2	1 (strongly disagree) to 7 (strongly agree)	“I think I should perform sun safe behaviours.”; “Performing sun safe behaviours is something I should do.”
Image Norms	5	1 (strongly disagree) to 7 (strongly agree)	“Celebrities and movie stars always seem to have a tan.”; “I see more examples of models who do not have a tan on TV and in magazines than I used to.” (reverse scored); “I think that to be a successful movie star or TV star you should have a tan.”; “It seems that society wants people to have a tan.”; “I can think of many movie stars and TV stars who do not have a tan” (reverse scored).
Tanning	2	1 (strongly disagree) to 7 (strongly agree)	“A person with a tan looks Australian”; “A person without a tan looks ‘Un-Australian”.
Responsibility	3	1 (strongly disagree) to 7 (strongly agree)	“I think it is my responsibility to perform sun safe behaviours”; “I think it is up to the government to ensure that sun safety measures are available” (reverse scored); “It is my personal choice to perform sun safe behaviours”.

Secondary outcome variables will assess the intervention’s effectiveness in improving participants’ attitudes toward sun protection; participants’ perceptions of normative support for sun protection (i.e. subjective norms, group norms, personal norms and image norms); and participants’ perceptions of control/self-efficacy toward sun protection (PBC). Additional constructs identified in previous research will also be examined, namely participants’ perceptions, as an Australian, of tanning and their perceptions of personal responsibility to engage in sun protection.

### Ethical considerations

The protocol of this paper was approved by the Queensland University of Technology Human Research Ethics Committee (approval number: 1200000658).

### Data analyses

Chi-square (categorical variables), ANOVA (normally distributed continuous variables), and Kruskal-Wallis tests (non-parametric variables) will be used to compare baseline characteristics between groups, as well as between those with complete data and those who withdrew or were lost to follow-up. Outcomes will be analysed using general linear models for each of the change outcomes, including the main effects of group and time and the interaction of group and time. Sensitivity analyses will be conducted to determine the effect of missing data.

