## Methods/Design

### Study design

The study is a three-armed prospective randomised controlled trial targeting approximately 420 males and females aged 18 years or older and living predominantly in the state of Queensland. An online intervention was considered to be potentially useful in this geographical area given that Queensland is a state where access to services is limited in regional and rural areas. Consenting participants will be randomised in a 200:200:20 ratio to (a) the intervention or (b) information only or (c) a control group using a computer-generated random number sequence. Randomisation will be undertaken by the consultant project web developers in association with the project investigator. Participants in each of the groups will complete three online assessments; at baseline, one week, and one month after the initial survey. Participants randomised to the intervention and information only groups will complete a brief survey immediately following completion of their respective conditions to measure each of the main study constructs.

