### Study sample

#### Sample eligibility criteria and recruitment procedures

Eligibility criteria will include male and female adults (aged 18 or over) living in Australia. Participants will be recruited from the community through university-based media releases, community billboards, newsletters, email lists, snowball sampling techniques, and the use of an existing database of participants from a previous sun safety study who consented to be contacted for participation in future studies.

Participants will receive an email and flyer providing information about the study and a link to the study website. Consent to participate will be obtained after participants are presented with a comprehensive outline of the study online and will involve participants clicking a box indicating that they agree to participate in the study. Participants will be randomised to a study condition immediately after completing Questionnaire 1. A link to the post-intervention questionnaires will be emailed to participants a week and then one month after the initial questionnaire.

Participants are advised that they will be eligible to receive an AUD $20 store voucher after completion of Questionnaire 1 and another AUD $20 store voucher after completing the two follow up questionnaires 1 week and 1 month later.

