#### Sample size

It is aimed to recruit a total of 420 participants (200 intervention/200 information only/20 control). Based on our previous research in the area, it is anticipated that there will be approximately 35% attrition over 4 weeks of follow-up for reasons such as failure to complete follow-up questionnaires. A total sample of approximately 260 (420–140) completing participants (130/group) is required to detect a medium effect in sun-protective behaviour. This sample size was determined by power analysis using the G*Power program [37,38]. Significance level (alpha) was established at 0.05 to avoid a Type 1 error, power (1–beta) was set at 95% to avoid a Type II error, and effect size was determined at .25. Therefore, for a 95% chance of detecting as significant a 4 week difference in sun safe behaviour, approximately 130 participants in each group are needed to complete the study.

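### Significance tests of baseline differences between randomised arms cannot show whether an imbalance matters, least of all for the 20-person control arm; describe baseline instead and fix a few covariates in advance (minor)

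*Protocol article*

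**What the plan says.** The Data analyses section assigns chi-square tests to categorical variables, ANOVA to normally distributed continuous variables, and states that "Kruskal-Wallis tests (non-parametric variables) will be used to compare baseline characteristics between groups". The same tests are to be applied "as well as between those with complete data and those who withdrew or were lost to follow-up", which is a different, non-randomised comparison.

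Three other statements bear on the point:

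- Timing (Sample eligibility criteria and recruitment procedures): "Participants will be randomised to a study condition immediately after completing Questionnaire 1".
- Allocation (Study design): "Consenting participants will be randomised in a 200:200:20 ratio".
- Variables: the Variables section lists eleven characteristics, beginning "Demographic data collected pre-intervention will include age (in years), sex (male or female), and postcode". The Table 1 scales are also available at baseline, since the Measures section says "The post-intervention questionnaires will assess the same constructs as Questionnaire 1".

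The outcome analysis is stated separately: general linear models for change outcomes, with group, time and their interaction. The article gives no significance level for the baseline tests and no rule for what follows from their results.

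**The concern.** A significance test asks whether a difference is more than chance would produce. Here participants are allocated after the baseline data are in, so the answer is known in advance provided the allocation was carried out properly. What the reader needs to know is different: how large the observed imbalance is, and whether the variable predicts the outcome. A p-value answers neither question, because it mixes the size of the difference with the size of the arms.

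The unequal allocation sharpens this. With 20 people, control can differ noticeably from the other arms on a prognostic variable without any test reaching significance. With several variables tested, a flag or two on unimportant differences is also unsurprising. The stated hypothesis covers superiority over control as well as over information only, so the make-up of those 20 people bears on a stated aim.

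**Working it through.** The article gives no figure for these tests, so there is none to reproduce.

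**Inputs.** Arm sizes of 200, 200 and 20 (Study design). Significance level of 0.05, which is an assumption: the article states it only for the power analysis ("Significance level (alpha) was established at 0.05 to avoid a Type 1 error"). Number of variables: eleven in the Variables section, or ten without postcode, plus ten Table 1 scales (two primary, eight others). Differences are in SD units, with approximate normality.

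**1. Chance range of a baseline difference.** The standard error of a difference in means is √(1/n₁ + 1/n₂).

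- Large arm versus control: √(1/200 + 1/20) = 0.235, and 1.96 × 0.235 = 0.46. The 95% range is ±0.46 SD.
- Intervention versus information only: √(1/200 + 1/200) = 0.10, and 1.96 × 0.10 = 0.20. The 95% range is ±0.20 SD.
- A gap above 0.3 SD between one large arm and control arises by chance for 20% of variables (0.3/0.235 = 1.28, two-sided).

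**2. Observed control gap at which the three-arm test turns significant.** Suppose the two large arms have equal means and control differs from them by d SD. The between-group sum of squares is d² × 20 × 400/420 = 19.05 d², on 2 degrees of freedom. The critical F(2, 417) at 0.05 is 3.017. Setting 19.05 d²/2 = 3.017 gives d² = 0.317 and d = 0.56 SD.

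**3. How often an observed imbalance is flagged.** In 400,000 simulated allocations at 200:200:20:

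| Control differs from at least one large arm by more than | Share of variables | Of these, flagged by the three-arm test |
|---|---|---|
| 0.25 SD | 36% | 12% |
| 0.3 SD | 26% | 16% |
| 0.5 SD | 5% | 61% |

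The shares exceed the 20% in step 1 because either large arm may differ from control. Moderate gaps mostly go unflagged; gaps above 0.5 SD are mostly flagged.

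**4. Chance flags.** Expected number = m × 0.05; probability of at least one = 1 − 0.95^m if the tests are independent.

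| Variables tested | Expected flags | At least one |
|---|---|---|
| 10 (listed characteristics without postcode) | 0.5 | 40% |
| 11 (with postcode) | 0.55 | 43% |
| 20 (the 10, plus Table 1 scales) | 1.0 | 64% |
| 21 (the 11, plus Table 1 scales) | 1.05 | 66% |

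**The case against.** The strongest reply is that nothing in the article hangs on these tests. They are said to compare the groups; no rule for declaring comparability or choosing covariates is written, and the outcome model is stated without reference to them. A reader might infer that the outcome comparison will be interpreted or adjusted according to which baseline p-values are significant. The text does not say so. This stands, and it limits severity.

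A reader might also infer that the tests are the only handling of baseline imbalance. They are not: analysing change with a group-by-time interaction refers each Table 1 scale to its own baseline. That stands for the scales. It does not cover imbalance in age, skin type or sun exposure.

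It is tempting to say that the tests will miss most real imbalances in control. Under sound randomisation there are no systematic shifts to miss, so power against a true shift is not the relevant measure. The supportable statement concerns observed gaps, as in steps 2 and 3.

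It is equally tempting to say that about one false flag will occur. That needs all 20 or 21 variables tested at 0.05. The article does not say that the Table 1 scales count as baseline characteristics, and even with 20 independent tests the chance of no flag is 0.95^20 = 36%.

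Sparse cells could be raised too: 20 controls over the five categories of "colour of skin before tanning (pale white skin, white skin, light brown skin, moderate brown skin, deep dark brown to black skin" average 20/5 = 4 per category. But the article does not say that this ordered variable will be tested by chi-square, it also offers Kruskal-Wallis, and handling of sparse cells is ordinary analysis-plan detail. I do not press it.

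Finally, the tests could serve as a check that allocation was executed properly. That is a legitimate use, but the article does not give it as the purpose, and it would not make a p-value a measure of comparability.

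**Conclusion.** The point holds as a minor one. The article names a method for comparing randomised arms at baseline that cannot tell the reader what matters, and the 20-person control arm makes it less informative still: control may differ from both large arms by up to about 0.56 SD without the three-arm test reaching significance. A non-significant result would therefore not show that control is comparable, and a significant one may be chance.

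The figures rest on the planned arm sizes, a 0.05 level that the article does not state for these tests, approximate normality, equal means in the two large arms for the 0.56 SD threshold, and independence for the chance-flag probabilities. Between intervention and information only the chance range is just ±0.20 SD, so the difficulty lies mainly with control. Deleting the tests would by itself change no outcome result.

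**What to change.** - Remove the between-arm significance tests from the Data analyses section. Keep the comparison of completers with those who withdrew or were lost, which is not a randomised comparison.
- Present baseline characteristics by arm with summary statistics and standardised differences.
- Add to the stated outcome models a short list of prognostic covariates, fixed before outcome data are seen and included whatever balance is observed. Age, sex, skin type, outdoor work hours and hours in the sun are examples; the investigators should choose the list.

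The variables are all in the first questionnaire, so no new data are needed. The cost is a change of wording and a few model degrees of freedom. The gain comes mainly from the covariates, since the stated model of group, time and interaction includes none.

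### The change-outcome model names no adjustment for the baseline score: unbiased, but less precise than the same data allow

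*Protocol article*

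**What the plan says.** The Data analyses section of the protocol article gives the outcome model in one sentence: "Outcomes will be analysed using general linear models for each of the change outcomes". The terms that the sentence goes on to name are group, time and their interaction. No baseline covariate is named, and none is ruled out. The term for change outcomes is not defined. It could mean computed differences from baseline, or change tested through the group-by-time interaction with baseline as one level of time.

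The same section says that chi-square, ANOVA and Kruskal-Wallis tests "will be used to compare baseline characteristics between groups". It does not link those tests to the outcome model.

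On timing, the recruitment section says "Participants will be randomised to a study condition immediately after completing Questionnaire 1". The Measures section says that the later questionnaires assess the same constructs as Questionnaire 1. A pre-randomisation score on intentions and on behaviour therefore exists for everyone randomised.

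The Sample size section fixes the planning values. On the test level it says "Significance level (alpha) was established at 0.05"; on power, "power (1–beta) was set at 95% to avoid a Type II error"; on the effect, "effect size was determined at .25"; and on the number of completers, "A total sample of approximately 260 (420–140) completing participants (130/group) is required". It gives no standard deviation and no correlation between baseline and follow-up.

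**The concern.** Subtracting baseline from follow-up sets the coefficient on baseline to exactly 1. With equal variances the best linear coefficient is r, which is below 1 for any outcome measured with error or changing over time. The difference score therefore carries baseline noise that a covariate would remove. Given the imbalance actually observed at baseline, it also over-corrects by (1 − r) times that imbalance.

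The ambiguity over change outcomes does not avoid this. With complete data, a group-by-time contrast between baseline and one follow-up is the same comparison of mean changes, again with the coefficient at 1.

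At stake are the width of the confidence intervals and the power for both primary outcomes. The small control arm is where this could matter most. The Background hypothesises that the intervention will do better than both the information-only and the control group, and only 20 participants are allocated to control.

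**Working it through.** **Inputs from the protocol article.** Alpha 0.05 (taken as two-sided), effect size 0.25 called medium (read as Cohen's f, which is d = 0.5 for two groups), 130 completers per group, 35% attrition, allocation 200:200:20.

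**Assumptions, not in the article.** Equal variances at baseline and follow-up (SD = 1), d expressed on the raw-score SD, one follow-up, and r between 0.3 and 0.9.

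**The plan's own figure.** A two-group ANOVA with f = 0.25, alpha 0.05 and power 95% needs 210 in total (105 per group). With 130 per group its power is 98.0%. Three equal groups would need 252. None of these is exactly 260, although 400 × 0.65 = 260. That mismatch is a separate matter. I take 130 per group as given.

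**Variance.**
- Change score: Var = 2(1 − r).
- Baseline-adjusted: Var = 1 − r² = (1 − r)(1 + r).
- Ratio, adjusted to change: (1 + r)/2. Variance saved: (1 − r)/2. SE saved: 1 − √((1 + r)/2).

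| r (assumed) | Var, change | Var, adjusted | Ratio | Variance saved | SE saved |
|---|---|---|---|---|---|
| 0.3 | 1.40 | 0.91 | 0.65 | 35% | 19% |
| 0.5 | 1.00 | 0.75 | 0.75 | 25% | 13% |
| 0.7 | 0.60 | 0.51 | 0.85 | 15% | 8% |
| 0.9 | 0.20 | 0.19 | 0.95 | 5% | 2.5% |

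A simulation with 130 per arm gave variance savings of 34.3%, 24.6% and 15.6% at r = 0.3, 0.5 and 0.7, in line with the formula. If two follow-ups are averaged under compound symmetry, the saving is 2(1 − r)/3, which is 47%, 33% and 20% at the same values.

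**Power for intervention against information only (130 v 130, d = 0.5).** SE = √(Var × (1/130 + 1/130)), with noncentral t. At r = 0.5 the SE is 0.124 for change and 0.107 adjusted, so d/SE is 4.03 and 4.65.
- r = 0.3: about 92% for change, 99% adjusted
- r = 0.5: about 98% and 99.6%
- r = 0.7: about 99.9% and nearly 100%

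**Power for intervention against control.** Control completers: 20 × 0.65 = 13. SE = √(Var × (1/130 + 1/13)). At r = 0.5 the SE is 0.291 for change and 0.252 adjusted, so d/SE is 1.72 and 1.98.
- r = 0.3: about 30% and 43%
- r = 0.5: about 40% and 50%
- r = 0.7: about 60% and 67%

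Only at r near 0.9 does this comparison reach about 97%, and there the two analyses hardly differ.

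**The case against.** The strongest reply is that the sentence comes from a condensed article, that its list of terms need not be complete, and that a fuller plan may add covariates. That stands in part: the article does not exclude baseline adjustment, so a reader should not infer that adjustment has been ruled out. The article does, however, state what is analysed and with which terms. The analysis as stated has the efficiency limit shown above.

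Three stronger readings are tempting, and the article does not support them.

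- A fixed loss of precision of 15–35%. That range is the variance saving for r from 0.7 down to 0.3 with one follow-up, and the article gives no r. At r = 0.8 to 0.9 the saving is 5–10%. The standard error, which sets interval width, changes by only about 8–19% even over r = 0.3 to 0.7.
- A serious loss of power in the main comparison. That requires a smaller effect than the planned one. At the article's own effect size, read as d = 0.5, both analyses are at about 92% or above for r of at least 0.3.
- A biased estimate, or baseline tests used in place of adjustment. Randomisation keeps the change analysis unbiased over repeated trials, and the article does not say that the baseline tests stand in for a covariate.

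It is also fair to say that the control arm is imprecise mainly because it is small, and that it lies outside the stated sample size of 130 in each of two groups. Adjustment helps that comparison but does not cure it.

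**Conclusion.** The point holds as one of efficiency, not validity. The stated model for change outcomes names no baseline covariate, although the score is available before randomisation for everyone. If the analysis is run as stated, its variance is larger than that of an adjusted analysis by a factor 2/(1 + r): 1.33 at r = 0.5 and 1.05 at r = 0.9.

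The practical gain is small for intervention against information only. It is moderate for intervention against control, where power stays low after adjustment for r from 0.3 to 0.7. These figures rest on equal variances, a single follow-up, an assumed r, and the reading of 0.25 as Cohen's f with d on the raw-score SD. The direction does not depend on the value of r: in large samples, baseline adjustment is never less efficient than the unadjusted change score.

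**What to change.** Replace the change-outcome wording with a model for the follow-up scores at Times 2 and 3, and at Time 1b for the two arms that have it. The terms would be group, time, group by time, the baseline score of the same outcome, and baseline by time. If the full plan already adjusts for baseline, one phrase in this section saying so would settle the point.

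Optionally, report baseline characteristics by arm descriptively instead of testing them. This is a secondary reporting matter that does not affect the estimate. The comparison of completers with those lost to follow-up can stay.

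The cost is a change of wording. It needs no new data, visits or participants.
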